## Abstract

**Background:**

Compelling evidence shows that appropriate use of anticoagulation in patients with nonvalvular atrial fibrillation reduces the risk of ischaemic stroke by 67% and all-cause mortality by 26%. Despite this evidence, anticoagulation is substantially underused, resulting in avoidable fatal and disabling strokes.

**Methods:**

DESPATCH is a cluster randomised controlled trial with concealed allocation and blinded outcome assessment designed to evaluate a multifaceted and tailored implementation strategy for improving the uptake of anticoagulation in primary care. We have recruited general practices in South Western Sydney, Australia, and randomly allocated practices to receive the DESPATCH intervention or evidence-based guidelines (control). The intervention comprises specialist decisional support via written feedback about patient-specific cases, three academic detailing sessions (delivered via telephone), practice resources, and evidence-based information. Data for outcome assessment will be obtained from a blinded, independent medical record audit. Our primary endpoint is the proportion of nonvalvular atrial fibrillation patients, over 65 years of age, receiving oral anticoagulation at any time during the 12-month posttest period.

**Discussion:**

Successful translation of evidence into clinical practice can reduce avoidable stroke, death, and disability due to nonvalvular atrial fibrillation. If successful, DESPATCH will inform public policy, providing quality evidence for an effective implementation strategy to improve management of nonvalvular atrial fibrillation, to close an important evidence-practice gap.

**Trial registration:**

Australia and New Zealand Clinical Trials Register (ANZCTR): ACTRN12608000074392

## Background

### An evidence-practice gap

Nonvalvular atrial fibrillation (NVAF) is a common arrhythmia of the heart that increases the likelihood of stroke and transient ischaemic attack (TIA), through clot embolism to large arteries of the brain [1]. NVAF is more prevalent with increasing age, affecting 1 in 20 people over the age of 65 and 1 in 10 over 75 [2]. Overall, NVAF accounts for 15% of stroke cases but as many as 20% of strokes in those aged 70 to 79 years and 30% of strokes in people aged 80 to 89 years [2,3]. The risk of stroke associated with NVAF depends on the presence of other stroke risk factors. A commonly used algorithm, called the CHADS2 score (congestive heart failure (CHF), hypertension, age over 75 years, diabetes and either prior stroke or TIA) [4], has been recommended to calculate the stroke risk in NVAF [5]. One point each is assigned for the presence of CHF, hypertension, age over 75 years and diabetes and two points for either prior stroke or TIA. Predicted annual stroke risk varies from 1.9% for a CHADS2 score of 0 to 18.2% for a score of 6.

Over 20 years of evidence from several randomised controlled trials demonstrates the effectiveness of antithrombotics in reducing the risk of ischaemic stroke in NVAF [6,7]. Antithrombotic agents are classified as either anticoagulants (*e.g*., warfarin) or antiplatelets (*e.g*., aspirin or clopidogrel). Anticoagulation dosing with warfarin is usually adjusted (adjusted-dose warfarin), according to blood tests, to maximise the benefits of treatment and minimise bleeding risk. Compared with placebo or no treatment, adjusted-dose warfarin reduces the risk of ischaemic stroke in patients with NVAF by 67% in relative terms (95% confidence interval [CI], 54% to 77%) [6]. Warfarin also reduces all-cause mortality by 26% (95% CI, 3% to 43%) [6]. Aspirin, the most widely studied antiplatelet medication, is associated with a more modest relative risk reduction (RRR) for ischaemic stroke (21%; 95% CI, -1% to 38%) [6]. Head-to-head comparisons of stroke risk reduction favour adjusted-dose warfarin over aspirin (RRR = 52%; 95% CI, 41% to 62%) and newer antiplatelet treatments [6-8].

Until recently, the management of NVAF in the elderly (> 80 years) remained problematic. Existing trials had typically enrolled younger patients (average age 71 years), perceived as less vulnerable to the risks of iatrogenic haemorrhage on warfarin [6]. There was also uncertainty about whether the benefits of warfarin could be realised in the 'real-world' setting of primary healthcare, compared with trial settings in tertiary institutions.

The Birmingham Atrial Fibrillation Treatment of the Aged (BAFTA) trial demonstrated the benefits of warfarin in primary healthcare in the elderly, randomising patients with an average age of 81.5 years to receive either warfarin or aspirin [8]. Patients were recruited into the study by their primary healthcare physicians, who were also responsible for patient day-to-day management. After an average of 2.7 years of follow-up, results showed that warfarin reduced the risk of ischaemic stroke by 70% (95% CI, 37% to 87%) and the risk of any major vascular event, including any stroke, myocardial infarction, pulmonary embolus, and vascular death, by 27% (95% CI, 1% to 47%). The risk of any major haemorrhage, including haemorrhagic stroke, was similar between patients receiving warfarin or aspirin (1.9% per year vs. 2.0%). The BAFTA study confirmed that warfarin is more effective than aspirin in the elderly receiving routine care and can be as safe as aspirin in older patients managed in a primary healthcare setting.

### Previous studies and other work informing this trial

Despite this evidence, recent reports suggest that up to 50% of patients with NVAF are not prescribed anticoagulation [*e.g*., [9]. At the time of planning this study, no single intervention had been shown to improve the management of NVAF in primary healthcare and the uptake of appropriate antithrombotics when evaluated in a randomised controlled trial. In a randomised evaluation of a patient decision aid, McAlister *et al*. [10] reported an increase in antithrombotic prescribing at three months following the intervention. However, at 12 months, the rates of antithrombotic prescribing in the intervention group had reverted to baseline levels and did not differ from the control group. Ornstein *et al*. [11], in a multifaceted intervention targeting several cardiovascular risk factors in primary healthcare, including atrial fibrillation, evaluated the effect of audit and feedback and computerised guidelines and reminder systems for overcoming practical and organisational barriers. Anticoagulant prescribing decreased over time in the intervention group, and no significant differences in prescribing were observed at posttest between intervention and control groups. In a trial carried out in general practices in England, practices were randomised to receive locally adapted guidelines, one educational meeting delivered by local opinion leaders, educational materials, and an offer of one educational outreach visit (or academic detailing) to improve the management of TIA and atrial fibrillation [12]. This intervention did not increase compliance with antithrombotic prescribing guidelines; however, the outcome did not distinguish between prescribing for warfarin or aspirin. A nonrandomised study, carried out in Tasmania, Australia, demonstrated a promising effect of guideline dissemination followed by academic detailing visits to primary healthcare physicians in one region in Tasmania [13]. The prescribing and use of warfarin had significantly increased within the intervention region but not the control region. However, as this study did not employ a randomised design, it is unclear, whether or not this result was biased by confounding variables.

Studies suggest that strategies to improve the management of NVAF should address physicians' concerns about the risks of anticoagulation. Choudhry *et al*. [14] reported that physicians were less likely to prescribe warfarin for patients with NVAF after any one of their patients receiving warfarin was admitted to a hospital for a haemorrhage. Physicians were no more or less likely to prescribe warfarin, however, if any one of their patients with NVAF had been admitted to a hospital with an ischaemic stroke.

In our representative survey of 596 Australian primarycare physicians, known in Australia as general practitioners (GPs), the GPs appeared overly cautious in prescribing anticoagulation in the presence of any perceived risk of major and even minor bleeding, even where treatment benefits clearly outweighed the risk of harm [15,16]. A substantial proportion of GPs 'strongly agreed' or 'agreed' that they were 'often unsure whether or not to prescribe warfarin' and that 'it is hard to decide whether the benefits of warfarin outweigh the risks or vice versa' (30.0% and 38.4%, respectively). Other local surveys have indicated GP reluctance to prescribe anticoagulation for NVAF in the elderly or in the presence of perceived bleeding risks, which would not necessarily preclude anticoagulation on the available evidence [17,18].

Clinicians with perceived specialist knowledge in stroke prevention and atrial fibrillation may be effective educators and preceptors for improving clinical management of NVAF. Yet, such access to experts in stroke medicine seems limited. In our national survey, a significant proportion of Australian GPs were either 'dissatisfied' or 'very dissatisfied' with access to neurologists (51.8%), even in metropolitan settings (47.4%) ([name], [name], [name], unpublished data). Previous research has found that collaborative involvement of specialists with family physicians increases anticoagulation prescribing in patients, suggesting collaboration with specialists is an important factor in patient care [19].

We set out to develop and evaluate a multifaceted, educational intervention (DESPATCH) tailored to the self-identified needs of Australian GPs, recognising their high perceived risk of anticoagulant use and the likely value of building confidence in decision making. The intervention features peer academic detailing and educational and practice materials. A novel element is expert decisional support to promote the uptake of anticoagulation, using feedback from clinical experts in stroke medicine.

Our primary hypothesis is that a higher proportion of patients with NVAF whose GPs have been randomly allocated to receive the DESPATCH intervention will be prescribed oral anticoagulation medication compared with patients whose GPs are allocated to the control group.

## Methods

### GP recruitment

All GPs located in our local region, South Western Sydney, were selected from a commercial database containing the contact details of GPs in active practice [20]. We restricted the population to GPs practicing with up to five other GPs to avoid large medical centres where GPs, practice staff, and patients are more likely to be itinerant. GPs were located within postal codes of the geographically defined regions, known as Local Government Areas (LGAs), of Fairfield (population 190,657), Campbelltown (population 149,071), Camden (population 53394), Bankstown (population 182,178), Liverpool (population 176,903), Canterbury (population 139,985), and Marrickville (population 77,141) [21]. GPs were mailed a prenotification letter advising them that researchers from the Faculty of Medicine of the University of New South Wales were offering the opportunity to participate in an education program about stroke prevention in general practice. The letter advised GPs that a research nurse would phone their practice to arrange a practice visit to explain the study in detail and obtain written consent. This professional development program was accredited by the peak professional body representing GPs in Australia (The Royal Australian College of General Practitioners).

### Inclusion criteria

GPs were eligible only if their practice utilised an electronic register recording contact details for patients, their date of birth, and date of last consultation. GPs were required to use their electronic system for recording prescriptions to facilitate identification of patients with NVAF.

### Exclusion criteria

GPs who anticipated retiring or moving their practice within the next 12 months were ineligible to participate.

### GP questionnaire

Prior to randomisation, GPs completed a baseline survey based on a previous questionnaire administered by the research team [15,16] and others [22] to ascertain baseline knowledge and self-reported management of patients with atrial fibrillation.

### Recruitment of the patient cohort

The prevalence of atrial fibrillation is relatively low in patients over the age of 65 years [2,3]. As it was not feasible to search the records of all patients over the age of 65 years, a search strategy was applied to electronic prescribing records to identify patients before practices were randomised (Figure 1). The search strategy was limited to patients over the age of 65 years who had attended the practice within the last 12 months and had been issued prescriptions for medications commonly used to treat atrial fibrillation (Figure 1). This search strategy builds on work showing that selecting patients prescribed digoxin identifies patients with atrial fibrillation with high specificity (> 95%) [23,24]. In developing the search strategy, we piloted an earlier version in the practice of one GP not involved in the study and found that 85% of patients with a noted diagnosis of atrial fibrillation in their medical records were identified using medication search terms for current or past use of digoxin, amiodarone, sotalol, or warfarin.

**Figure 1 F1:**
[figure not shown]
**S****ummary of electronic search strategy**.

Before randomisation, GPs or a member of the practice perused the list of patients meeting our age and medication search criteria and removed patients who had died, had a life expectancy of less than 12 months, or were affected by dementia or significant cognitive impairment. Patients with insufficient English language skills or no longer visiting the practice were also removed from the list.

An 'opt-out' consent process was approved by the administering institution's human research ethics committee. Patients meeting search and inclusion criteria were mailed a letter on GP and University letterhead explaining that their GP was involved in a research study and that researchers were requesting to review their medical record. Patients declining permission were advised to notify research staff by completing a form to return to the researchers via a business reply paid envelope or to notify research or practice staff of their decision via phone.

### General practitioner randomisation and allocation concealment

After patients had been contacted, GPs were randomised by a statistician external to the research project to ensure allocation concealment, into one of two groups: DESPATCH or a waiting-list control. All GPs sharing the same practice address (group practices) were randomised as one cluster and randomisation occurred on the same day for all GPs (October 13, 2009). GPs were first stratified by LGA. Within each stratum, they were then ranked by practice size (*i.e*., the number of patients contacted at baseline) before being randomly allocated into one of the two arms of the study using computer-generated random numbers. Block randomisation with a fixed block size of two was used to minimise the discrepancy in sample size at the individual level.

### The DESPATCH intervention

This is a multifaceted, tailored educational intervention comprising components designed to redress barriers to the translation of best evidence into clinical practice relevant to the management of NVAF. The DESPATCH intervention includes decisional support to improve confidence in decision making. The intervention was delivered within 12 months of randomisation.

### Academic detailing

Medically trained peers were employed to deliver three academic detailing sessions via telephone. Prior to each of the three contacts, GPs received a mail out of resources from the research team (Figures 2,3,4). Resources included summaries of existing randomised controlled trials evaluating antithrombotic therapies, risk stratification using the CHADS2 score, information on common drug and food interactions with warfarin [25], and a patient decision aid adapted from an existing resource [26]. A patient question prompt sheet and a values-clarification exercise, modified from published resources [27,28], were included. All mailed materials were accompanied by a cover letter signed by [name], [name], NZ, and MG using electronic signatures.

**Figure 2 F2:**
[figure not shown]
**Outline of DESPATCH intervention and its delivery: first phase**.

**Figure 3 F3:**
[figure not shown]
**Outline of DESPATCH intervention and its delivery: second phase**.

**Figure 4 F4:**
[figure not shown]
**O****utline of DESPATCH intervention and its delivery: third phase**.

Each academic detailing session comprised standardised prompts related to the mailed materials addressing barriers to the use of anticoagulation in their practice. During each academic detailing session, GPs were invited to identify a patient with atrial fibrillation about whose management they wish to receive specific feedback. The medical peers used a standardised pro forma for each GP-identified patient, requesting and recording information from GPs about patient medical history, stroke risk factors, current antithrombotic treatments, adverse events on antithrombotics, and any reasons for not prescribing anticoagulants. Academic detailers were instructed to calculate the CHADS2 score and provide evidence-based feedback using standardised information on antithrombotic treatment.

### Expert decisional support

After each academic detailing session, medical peers returned completed pro formas to the research team. On behalf of the GPs, the research team sought feedback from experts about the management of these patients. Experts comprised medical specialists in neurology and cardiology. Information from each de-identified completed pro forma was summarised onto one page. For each patient, a CHADS2 score and annual ischaemic stroke risk were reported. The one-page summary was emailed to specialists to provide written feedback, and this feedback was then mailed to GPs via the research team (Additional File 1).

During the development of our intervention, another team published a protocol for a cluster randomised controlled trial (cRCT) in primary care, evaluating a faxed one-page evidence-based statement referring to specific patients, with or without the signatures of local 'opinion leaders' [29]. The protocol provided a model for delivering this aspect of the intervention.

### Seminars

GPs in the intervention were invited to a workshop delivered by [name]. The workshop summarised current evidence on antithrombotic medication, risk stratification for patients with NVAF, and a discussion of barriers to the wider use of anticoagulation. Case studies were used to illustrate evidence-based patient management. The workshop was based on a published education module authored by [name] and MG for the National Stroke Foundation of Australia [30].

GPs randomised to the control group received evidence-based guidelines [31,32] by mail and were invited to a seminar delivered by [name] about a topic in cardiology unrelated to atrial fibrillation.

### Follow-up

We define our follow-up period as the 12-month interval following the date practices were randomised (October 13, 2009).

## Outcome assessment by medical record audit

In a blinded, independent medical record audit, research nurses will collect data to enable our assessment of the outcomes. Nurses will locate records of patients identified by the search strategy applied prior to randomisation, excluding records of patients who had refused permission. For cost and ethical reasons, auditing of posttest and baseline data is to be carried out after the intervention has been delivered. Auditing at posttest avoids the ethical dilemma of withholding feedback about suboptimal practice before completion of the study. Nurses carrying out data collection have not previously been involved with the project and will be employed through a company supplying contracted health services staff.

## Quality assurance of medical record audit

Depending on available resources, we aim to repeat the audit process in a random sample of between 5% to 10% of practices, obtaining estimates of inter- and intrarater reliability.

## Ascertainment of atrial fibrillation

Using a standardised audit form, the trained nurse auditors, blinded to the study design, aims, and group allocation, will apply a standardised checklist to first determine whether or not a patient has a recorded diagnosis of atrial fibrillation.

Any diagnosis of atrial fibrillation noted in the medical record, appearing in specified test results (electrocardiograms, Holter monitoring, and transesophageal or transthoracic echocardiograms), referral letters, specialist correspondence, or hospital discharge summaries, will identify patients as having atrial fibrillation. The date of the recorded entry, correspondence, or test result will be noted. In the absence of a diagnosis of atrial fibrillation, atrial flutter will be recorded where noted in the medical record.

For the purposes of distinguishing between cases of atrial fibrillation (or atrial flutter) first noted before or after randomisation, nurses are instructed to exhaust the standardised checklist and proceed through a set of instructions directing them to note if atrial fibrillation was diagnosed on or after a chosen date (October 1, 2009), approximating the date of randomisation on October 13, 2009. Patients whose diagnosis of atrial fibrillation was noted only after randomisation will be considered 'newly diagnosed' and excluded, minimising the possibility of biased patient selection postrandomisation. To maintain blinding of the study design and aims, nurses are informed that one of the project aims is to distinguish between newly diagnosed and established cases of atrial fibrillation (or atrial flutter) to determine the incidence of newly diagnosed cases over a period of 12 months. Nurses are instructed to collect data on all cases of atrial fibrillation (or atrial flutter), irrespective of when the diagnosis was noted.

When collecting information about comorbidities (see below), nurses will also record diagnoses of mitral stenosis, mixed mitral valve disease, rheumatic mitral valve disease, or mitral valve replacement, allowing the researchers to exclude these cases as examples of valvular atrial fibrillation. Cases of atrial flutter, in the absence of a recorded diagnosis of atrial fibrillation, will be regarded as equivalent to a diagnosis of atrial fibrillation in keeping with international evidence-based guidelines recommending identical management of these cardiac arrhythmias [5].

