### Losses to follow-up

Patients identified as having atrial fibrillation without any recorded contact with GPs during the follow-up period will be considered lost to follow-up. The proportion of patients lost to follow-up or with partly completed follow-up will be compared across groups.

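### Death and departure are screened only before the randomisation day, so patients already dead or gone on 13 October 2009 stay in the cohort and are counted as losses to follow-up

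*Protocol article*

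**What the plan says.** **Screening for death and departure.** Under Recruitment of the patient cohort, the GP or practice staff went through the search list before randomisation and "removed patients who had died, had a life expectancy of less than 12 months, or were affected by dementia or significant cognitive impairment". In addition, "Patients with insufficient English language skills or no longer visiting the practice were also removed from the list". Opt-out letters were then posted.

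**Randomisation.** The section on randomisation and allocation concealment gives the order: "After patients had been contacted, GPs were randomised by a statistician external to the research project to ensure allocation concealment". All GPs were randomised on 13 October 2009, and Follow-up starts the 12 months on that date.

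**Audit cohort.** Under Outcome assessment by medical record audit, "Nurses will locate records of patients identified by the search strategy applied prior to randomisation, excluding records of patients who had refused permission". Ascertainment of atrial fibrillation then takes out valvular cases and new diagnoses. Nothing takes out patients who died or left before 13 October.

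**Losses.** Under Losses to follow-up, patients with atrial fibrillation "without any recorded contact with GPs during the follow-up period will be considered lost to follow-up". The sensitivity section on losses reruns the primary outcome twice: without patients with missing data, and with missing follow-up scored as not anticoagulated. The secondary outcome on percentage of time gives patients with no anticoagulation note zero days over a fixed 365-day denominator.

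**Diagnosis date.** Nurses note whether atrial fibrillation was "diagnosed on or after a chosen date (October 1, 2009), approximating the date of randomisation on October 13, 2009". The exclusion rule follows: "Patients whose diagnosis of atrial fibrillation was noted only after randomisation will be considered 'newly diagnosed' and excluded".

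**The concern.** Time zero is 13 October 2009, but vital status and attendance were last checked at some earlier point, which may differ from practice to practice. A patient who died or moved in between was never at risk of the outcome, yet the stated rules keep that patient in the cohort.

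Two things are at stake:

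- **Dilution.** Where such patients score as untreated, the observed proportion falls in both arms and so does the difference between them.
- **Reporting.** The loss-to-follow-up figure, which the article promises to compare between arms, would include people who had no follow-up to lose.

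The diagnosis date raises a smaller question. The nurses' flag and the exclusion rule use dates 12 days apart, and the article does not say in words which one settles a diagnosis first recorded on 1 to 12 October.

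**Working it through.** **1. The plan's own sample size.** Inputs from Sample size: 50% vs 60%, 80% power, 5% level (two-sided assumed), ICC 0.04, 25 patients per practice, 10% loss.

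- Uncorrected: n' = [1.96√(2 × 0.55 × 0.45) + 0.842√(0.25 + 0.24)]² / 0.10² = 387.3.
- With continuity correction: n = (n'/4)[1 + √(1 + 4/(n' × 0.10))]² = 407.1, against 407 stated.
- Design effect: 1 + 24 × 0.04 = 1.96. Then 407 × 1.96 = 797.7, so 798, and 798/0.9 = 886.7, so 887.

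The stated figures reproduce.

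**2. How many patients could be affected.** Share f = annual rate × months/12. The article gives neither the interval nor a rate of death or departure, so both are assumptions.

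- Low end: 5% a year for 1 month gives f = 0.42%, about 4 per 1,000.
- High end: 10% a year for 6 months gives f = 5%, or 50 per 1,000.

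**3. Dilution where they are scored as untreated.** The difference becomes 60(1 − f) − 50(1 − f) = 10(1 − f) points: 9.96 at the low end and 9.5 at the high end (57% vs 47.5%).

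**4. Power at the planned 887 per group.** The rerun that scores missing follow-up as untreated keeps these patients in, so the effective size is 887/1.96 = 452.6 per group. Design effect held at 1.96, with no other losses scored as untreated:

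| Case | Uncorrected | Continuity-corrected |
|---|---|---|
| No such patients | 85.7% | 84.2% |
| 0.42%, scored untreated | 85.4% | 83.8% |
| 5%, scored untreated | 81.7% | 79.9% |
| 5%, excluded | 83.9% | 82.2% |

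Excluding them recovers about half of what is lost at the high end.

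**5. Percentage of time on treatment.** Most of these patients enter as zero days. There is an exception: use noted in the three months before randomisation is carried to that date and runs for three months from the last note. Taken literally, a patient with an INR on 20 August who died on 1 September, with no suspension recorded, would be credited until about 20 November, which is 38 days after randomisation.

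**6. Diagnosis date.** From 1 to 13 October is 12 days. If 5% to 20% of the cohort were first diagnosed in any one year (assumed), 1,000 × 0.05 × 12/365 to 1,000 × 0.20 × 12/365 gives 1.6 to 6.6 patients per 1,000 in that window.

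**The case against.** **The harm is limited and partly handled.** The gap precedes allocation, so no bias between arms is expected. One of the two reruns drops patients with missing data. The list review also removed people with a life expectancy under 12 months, so early deaths should be fewer than average. All of this stands, and it is why the size is put as mild.

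**This is detail a condensed article leaves out.** That would be fair if the article were silent. It states the screening, audit and loss rules, however, and these together place the patients in the wrong category.

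**A reader might infer a real loss of power, to about 76%.** The documents do not support that. At an effective 407 per group with 5% scored as untreated, power is 75.4% corrected or 77.5% uncorrected. But 407 is the effective size after the 10% loss has been taken off, while the rerun keeps these patients in. Nor is the 10% an annual rate of death or departure: it covers the whole study and includes ordinary loss to follow-up. If genuine losses brought the total scored as untreated to 10% (54% vs 45%), uncorrected power would be 77.4%, but that belongs to the rerun's deliberately adverse assumption, not to this gap alone.

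**A reader might infer that diagnosis is cut at 1 October, so that eligible patients are dropped.** The exclusion is worded by randomisation, the date of each entry is noted, and data are collected on every case whenever diagnosed. No eligible patient is dropped by the written rule. Nor can a flag set before randomisation let later diagnoses in.

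**The repair is not free.** The listed audit items include no date of death or departure. Departure judged after the intervention, from missing contact in records kept by unblinded GPs, could bring in the bias the trial has avoided. Both points stand and shape the fix.

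**Conclusion.** The concern holds for death and departure. As written, patients who died or left between the list review and 13 October 2009 remain in the cohort and are reported as lost to follow-up. They count as untreated in one sensitivity rerun and usually as zero days of use in the time-on-treatment outcome.

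The consequence is slight dilution, similar in both arms, and an inflated loss figure. About 4 to 50 patients per 1,000 are involved, resting wholly on an assumed gap of 1 to 6 months and an assumed 5% to 10% a year. At the top of that range the planned 10-point difference becomes 9.5 points and power at 887 per group stays at about 80% (79.9% or 81.7%, depending on the continuity correction). The same 5% would equal half of the 10% loss allowance, so the reported loss rate is where the distortion would show most.

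The diagnosis date needs only a sentence of clarification.

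**What to change.** 1. Define the analysis cohort at 13 October 2009. In both arms, and blinded to allocation, exclude patients with a dated record of death or transfer out before that day.
2. Report their number by arm, separately from losses to follow-up.
3. Do not infer departure from absence of contact after randomisation. Patients without a dated earlier exit stay in and are handled as losses, as now.
4. State that the recorded diagnosis date, compared with 13 October 2009, decides who is newly diagnosed, and that the 1 October flag is a prompt for the nurses only.

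The cost is one extra date on the audit form and a slightly smaller cohort. The Discussion says that data collection has begun, so records already audited would need a second look for that date. Because the deciding entries predate allocation, removing these patients should not unbalance the arms.
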